### Cost-effectiveness

Incremental cost will be calculated and, by using incremental QALYs and GAS scores, expressed as the incremental cost-utility ratio (ICUR) and incremental cost-effectiveness ratio (ICER), respectively. The ICUR and ICER will be measured for both intervention groups. ICUR represents the costs required for the particular intervention to generate one additional QALY in comparison with care as usual (control group). ICER represents incremental costs per relevant achievement of work-related treatment goals (GAS) over a time period of 6 months. Both ratios will be estimated by bootstrap analyses. As an indication of whether an intervention will be considered cost-effective, the ICUR is compared to a range of ceiling ratios varying from €20k per QALY to €80k per QALY in the Netherlands, with €30k per QALY commonly accepted as the prevailing ceiling ratio. In addition, cost-effectiveness acceptability curves will be used to inform decision-makers on the probability that the cognitive rehabilitation program is cost-effective.

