In the current study, we will develop both a basic and an extensive version of an Internet-based cognitive rehabilitation program for occupationally active cancer survivors with persistent cognitive problems. The intervention consists of different elements from meta-cognitive strategy training that have been shown to be effective in managing symptoms, such as problems related to memory, concentration, attention and executive functioning, and fatigue. In this article, we describe the design of a randomized, controlled, multicenter trial in which the (cost-)effectiveness of this Internet-based cognitive rehabilitation program on work-related outcomes will be evaluated. It is hypothesized that both cancer survivors who undergo the basic or extensive cognitive rehabilitation program will achieve more often their pre-set work-related rehabilitation goals, compared to cancer survivors in the waitlist control group. Furthermore, it is hypothesized that cancer survivors with cognitive impairment at study entry (as measured with neuropsychological tests) will be better at achieving their pre-set rehabilitation goals when allocated to the extensive cognitive rehabilitation program compared to the basic cognitive rehabilitation program. Finally, we hypothesize that both the basic and extensive cognitive rehabilitation program will be cost-effective compared to the control group. If found to be (cost-)effective, this Internet-based cognitive rehabilitation program can be embedded as standard practice in the growing community of occupationally active cancer survivors experiencing cognitive problems at work.

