In this study, GAS will be used as the primary study endpoint, evaluating between-group differences over time in GAS scores. The GAS scores will be calculated according to published scoring algorithms (see the “Methods/design” section). To evaluate intra-individual differences in the trajectory of change over time for the primary outcome, we will use a growth curve modeling approach with random intercept and slope. This approach takes into account the within- and between-person variability and deals adequately with missing data [51]. Both linear and quadratic effect of time will be modeled to determine if an initial improvement or deterioration in the outcome was followed by a deceleration of this change over time. Appropriateness of the final model (with or without quadratic effect) will be determined based on model fit statistics: the Bayesian information criterion [52] and the Akaike information criterion [53]. In all analyses, the control group will be the reference group. Furthermore, moderation analysis will be conducted to determine whether the interventions have a differential effect among the subgroups classified as cognitive impaired yes or no (measured by ACS) at baseline. Baseline differences will be accounted for in the model. In case of non-ignorable dropout, we will correct the model for different patterns of missing values [54]. All analyses will be done on an intention-to-treat basis. Furthermore, as a secondary analysis, per-protocol analyses will be performed on patients who met criteria for minimal compliance (i.e., at least 4 logins into the online program) with the intervention(s). Differences in mean change scores over time between the intervention groups and the control group will be accompanied by effect sizes. Effect sizes of 0.2 are considered small, 0.5 moderate, and 0.8 large [55]. Effect sizes of approximately 0.5 are considered to be clinically relevant [56].

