## Discussion

In the current study, we will evaluate the (cost-)effectiveness of both a basic and an extensive version of an online cognitive rehabilitation program on work-related goal attainment, subjective cognitive functioning, work ability, work functioning, absenteeism and presenteeism, need for recovery, and quality of life.

Our study has the following notable strengths: (1) the randomized trial design, (2) the multicenter nature of the trial, (3) the comparison of two intervention groups with a waiting list control group, (4) the selection of patients based on the presence of cognitive problems, (5) the use of a personalized treatment outcome (GAS) to capture meaningful work-related outcomes; and (6) the inclusion of a cost-effectiveness analysis and process evaluation.

Despite these strengths, some shortcomings should be taken into account. First, the basic version of the cognitive rehabilitation program differs from the extensive version in two respects, namely, content and therapy guidance. It might be the case that one of the versions is more or less effective than the other. If so, distinguishing between the efficacy of those two respects is not possible. However, we have chosen this design with this limitation, as it gives us the opportunity to examine if a low intensive, parsimonious approach that can be easily implemented and is inexpensive might be sufficient to treat cognitive problems in occupationally active cancer survivors, or that a more extensive approach is needed for (a subgroup of) patients. Second, although the use of the personalized treatment outcome (GAS) is a major strength, it comes with disadvantages as well. Two of those issues are (1) its lack of a clear guide in how to interpret the aggregated GAS *T*-score and (2) challenges in defining realistic and solid GAS scales. To overcome the first issue, GAS scores will be accompanied by effect sizes so that it will be appropriate to draw conclusions about effectiveness. With regard to the second issue, we will train the involved therapists in the use of GAS. Besides, an independent assessor will perform quality checks on the use and scoring of GAS during the initial phase of the trial.

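### The cost-utility ratio of each programme is defined against control and no extensive-versus-basic economic comparison is stated, so the extensive programme can pass the ceiling although its extra cost over basic does not

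*Protocol article*

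**What the plan says.** The analysis is described in the Cost-effectiveness section that follows Statistical analysis in the protocol article.

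- **Which ratios:** "The ICUR and ICER will be measured for both intervention groups".
- **Comparator of the ICUR:** the cost of "one additional QALY in comparison with care as usual (control group".
- **Comparator of the ICER:** none is named. The sentence reads "ICER represents incremental costs per relevant achievement of work-related treatment goals (GAS) over a time period of 6 months".
- **Yardstick:** as an indication of cost-effectiveness, "the ICUR is compared to a range of ceiling ratios varying from €20k per QALY to €80k per QALY", with EUR "30k per QALY commonly accepted as the prevailing ceiling ratio".
- **Uncertainty:** both ratios are bootstrapped. Acceptability curves are planned for the rehabilitation programme, without saying which options enter them.

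Two other places bear on the comparator. The last paragraph of the Background gives the economic hypothesis that "both the basic and extensive cognitive rehabilitation program will be cost-effective compared to the control group". The Discussion defends a design in which the two programmes differ in both content and guidance on the ground that it allows the team to "examine if a low intensive, parsimonious approach that can be easily implemented and is inexpensive might be sufficient", or to find that a fuller approach is needed, possibly for a subgroup.

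**The concern.** A patient receives one of three options: no programme for now, basic, or extensive. For mutually exclusive options, the ratio that informs the choice sets each option against the next less costly one that is not dominated. A ratio of extensive against control pools two steps: from control to basic, and from basic to extensive. If the first step is good value, it can carry the second under the ceiling.

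The second step has a foreseeable price. According to the Intervention section, only the extensive arm has therapy guidance, and the first Cost-effectiveness section, among the study measures, costs professional time per patient.

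At stake is the economic side of the question that the Discussion asks. Read as written, the ICUR rule can label both programmes cost-effective and give no warning that the guidance and strategy modules cost more per added QALY than the ceiling allows.

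**Working it through.** The document gives no costs or QALYs by arm, so there is no figure of the plan to reproduce. Only the ceilings come from it: EUR 30k, with a range of EUR 20k to 80k. All arm-level values below are assumptions.

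**Notation.** cB, qB and cE, qE are the mean extra cost and QALY of basic and extensive over control; L is the ceiling. Net monetary benefit (NMB) = L × q − c. Assume cE > cB.

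**General result.**
- Extensive passes against control if cE/qE ≤ L, that is, qE ≥ cE/L.
- Extensive passes against basic if L × (qE − qB) ≥ cE − cB, that is, qE ≥ qB + (cE − cB)/L.
- The second threshold minus the first is qB − cB/L = (L × qB − cB)/L = NMB of basic divided by L.

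This gap is positive whenever basic is itself cost-effective against control, which is what the Background hypothesises. For gains inside the gap, extensive passes against control but the step up from basic does not.

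**Illustration at L = EUR 30,000.** Basic: +EUR 200, +0.010 QALY. Extensive: +EUR 700, +0.025 QALY.
- Basic versus control: 200/0.010 = EUR 20,000 per QALY.
- Extensive versus control: 700/0.025 = EUR 28,000 per QALY.
- Extensive versus basic: (700 − 200)/(0.025 − 0.010) = 500/0.015 = EUR 33,333 per QALY.
- NMB of basic: 300 − 200 = EUR 100. NMB of extensive: 750 − 700 = EUR 50. Basic is the better choice.
- The gap runs from 700/30,000 = 0.0233 to 0.010 + 500/30,000 = 0.0267 QALY. Its width is 0.0033 = 100/30,000.

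**Dependence on the ceiling.** With these figures the two readings disagree only for ceilings between EUR 28,000 and EUR 33,333. At EUR 40,000, basic has NMB 400 − 200 = EUR 200 and extensive 1,000 − 700 = EUR 300, so extensive is preferred.

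**Range over other assumed values, at EUR 30,000.**

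| cB (EUR) | qB | cE (EUR) | Passes vs control from qE | Passes vs basic from qE |
|---|---|---|---|---|
| 100 | 0.010 | 400 | 0.0133 | 0.0200 |
| 100 | 0.010 | 800 | 0.0267 | 0.0333 |
| 50 | 0.005 | 400 | 0.0133 | 0.0167 |
| 200 | 0.020 | 600 | 0.0200 | 0.0333 |

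In the first row:
- With qE = 0.015, the ratios against control are 100/0.010 = EUR 10,000 and 400/0.015 = EUR 26,667, while extensive versus basic is 300/0.005 = EUR 60,000.
- With qE = 0.025, extensive versus basic is 300/0.015 = EUR 20,000 and there is no conflict.

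**The case against.** The strongest reply is that the section is one paragraph of a condensed article. Ordering of arms, dominance checks and the layout of acceptability curves are commonly left to a fuller document, and defining a ratio against usual care does not exclude a further one. The plan also matches its own economic hypothesis, which is about control. With a common control, the point estimate of extensive versus basic follows by subtracting the planned increments, as the arithmetic above does.

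Much of this stands, and it rules out several stronger readings that a reader might infer:

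- **That the plan excludes an extensive-versus-basic ratio.** It does not. It states none.
- **That the ICER is also fixed against control.** Its sentence names no comparator. Control is an inference from the hypothesis. The sentence "In all analyses, the control group will be the reference group" adds little, because it stands in the paragraph on the growth model for goal attainment, and a reference category does not bar a contrast between the active arms.
- **That the design question goes unanswered.** On effectiveness it is addressed. The Background has a hypothesis of extensive versus basic in impaired patients, Statistical analysis plans moderation by impairment, and the sample size is inflated for that subgroup analysis.
- **That the plan would recommend the dearer programme.** The ceiling comparison is offered as an indication, and no rule for choosing between programmes is given.

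What does not stand is that this is only missing detail. The text states a comparator and a yardstick for the ICUR, and that pair is inadequate for choosing among three options. Subtraction gives a point estimate but not its uncertainty, and nothing in the plan calls for it.

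**Conclusion.** The point holds for the economic evaluation, and explicitly so for the ICUR. Applied as written, the rule can pass both programmes while the added cost per QALY of extensive over basic lies above the ceiling. The range of extensive-arm gains in which this happens has width equal to basic's net monetary benefit divided by the ceiling. In the assumed sets above that is 0.0033 to 0.0133 QALY at EUR 30k.

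The wrong conclusion is possible, not certain. It requires that basic is cost-effective against control, that extensive costs more than basic, and that the extensive gain falls inside that range. It also depends on the ceiling: EUR 33,333 fails at EUR 30k but lies within the EUR 20k to 80k range and passes at EUR 40k. The effectiveness analyses are unaffected.

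**What to change.** In the Cost-effectiveness analysis section:

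1. Add a full incremental analysis: order the three arms by mean cost, check for dominance and extended dominance, and report the ICUR and ICER of extensive versus basic with bootstrap uncertainty.
2. Name the comparator of the ICER.
3. Draw the acceptability curves for all three arms jointly, from net monetary benefit in the same bootstrap samples.
4. Keep each programme's comparison with control, which serves the stated hypothesis.

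The costs and EQ-5D-5L data are already planned, so no extra patients or measurements are needed. The price is a little more analysis work and a less precise extra comparison, since the difference between two active programmes is likely to be small relative to its uncertainty. Stating this before results are known also removes any later choice of comparator.

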## Methods/design

### Study design

A multicenter, three-armed randomized controlled trial will be conducted to evaluate the effectiveness of an online cognitive rehabilitation program. Two intervention groups (i.e., a basic and an extensive cognitive rehabilitation program) and one waitlist control group will be included. An economic evaluation will be conducted to assess cost-effectiveness of the cognitive rehabilitation program. Furthermore, a process evaluation will be performed to evaluate the procedures regarding recruitment, execution and implementation of the cognitive rehabilitation program. This study will be conducted by the Netherlands Cancer Institute, Amsterdam, the Netherlands. Participants will be cancer survivors who are treated for cancer in several (university) hospitals in the Netherlands. The study has been approved by the Medical Ethic Committee at the Netherlands Cancer Institute and is registered at ClinicalTrials.gov (registration number NCT03900806).

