### Recruitment and randomization

Cancer patients will be identified through the Netherlands Cancer Registry and recruited via treating physicians of several (university) hospitals in the Netherlands. Potentially eligible patients will receive a personalized letter from their treating physician, informing them about the study and the cognitive rehabilitation program. Patients will be asked to respond via post (response card), email, or phone whether or not they are interested in participation. In case a patient does not respond, a reminding letter will be sent after 3 weeks. Patients who express interest in participation will receive a phone call from the study team for further screening (e.g., a check of their employment status) and to provide additional information about the trial. Patients will be invited by e-mail to complete the baseline measurement (i.e., an online questionnaire and an online neuropsychological assessment) in case they fulfill all criteria, are motivated, and are willing to comply to the trial procedures. After completion of this baseline measurement, a session (face-to-face or using videoconference) with a therapist (e.g., neuropsychologist, occupational therapist) will be planned to discuss outcomes of the neuropsychological assessment, followed by collaborative treatment goal setting.

Upon receipt of all baseline information and after the session with the therapist, patients will be randomly allocated to the basic intervention arm (*N* = 87), the extensive intervention arm (*N* = 87), or the waitlist control group (*N* = 87), using randomized design in the computerized program ALEA. Minimization will be applied for the presence of cognitive impairment on the neuropsychological assessment to equalize group sizes. Blinding of participants and professionals is not possible for this type of intervention. Further, blinding for assessment is not applicable since measurements will be computer-based. A flow diagram of the recruitment procedure is outlined in Fig. 1. Figure 2 shows a schedule of enrolment, interventions, and assessments.

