#### Waiting list control group

Participants in the waiting list control group will be offered the opportunity to follow the basic cognitive rehabilitation program after completion of the 26-week follow-up measurement.

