#### Primary outcome measure

The primary outcome for this study will be individually defined work-related treatment goals, using the 6-point Goal Attainment Scale (GAS) on personal outcome (− 3, achievement of the goal after training is worse; − 2, achievement of the goal is the same; 1, partial achievement of the goal; 0, achievement of the goal; 1, exceeding the goal; and 2, greatly exceeding the goal) [33]. Patients will formulate three treatment goals and define the six outcome levels at baseline, in collaboration with their therapist. Attainment of the goals is measured in a standardized way, i.e., an overall GAS *T*-score will be computed for each participant on the basis of aggregated GAS scores involving attainment of multiple personal treatment goals, according to a summary scoring algorithm that calculates the extent to which patients’ goals are met.
$$ T=50+\frac{10\sum {w}_i{x}_i}{{\sqrt{\left(1\hbox{-} \rho \right)\kern0.5em \sum {w_i}^2+\rho \left(\sum {w}_i\right)}}^2} $$

*T* is the composite score, *w*_*i*_ is the weight assigned to goal_*i*_ (based on the patients prioritization), *x*_*i*_ is the original score for goal_*i*_ ranging from − 3 to + 2, and *ρ* is the estimated correlation between goal scores. The *T*-score has a mean of 50 and a standard deviation of 10. *w*_*i*_ is considered as equally relevant for each goal and thus assigned 1. Based on previous studies, correlation between the goal scores is constant and can be set at 0.3 [33]. Goals will be set at baseline (T0), and evaluated by patients (of all study arms) in collaboration with the cognitive therapist at T1 and T2. Due to practical reasons, this scoring of the level of attainment will be done by telephone. An independent assessor will perform quality checks on the use and scoring of GAS during the initial phase of the trial, to assure fidelity of the GAS-protocol.

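### The cost-utility ratio is labelled as programme versus usual care, but the control arm is a waitlist that has already had assessment, therapist feedback and goal setting

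*Protocol article*

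**What the plan says.** In the protocol article, the Cost-effectiveness section that follows Statistical analysis expresses the ICUR as cost per additional QALY "in comparison with care as usual (control group". The result is to be read against ceilings of EUR 20k to 80k per QALY, with EUR 30k as the usual one, and acceptability curves are to inform decision-makers.

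Elsewhere the same arm is described differently. Study design says: "Two intervention groups (i.e., a basic and an extensive cognitive rehabilitation program) and one waitlist control group will be included". Under Waiting list control group, its members "will be offered the opportunity to follow the basic cognitive rehabilitation program after completion of the 26-week follow-up measurement". Usual care is not defined.

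Recruitment and randomization has every eligible patient "complete the baseline measurement (i.e., an online questionnaire and an online neuropsychological assessment"). A therapist session is then planned "to discuss outcomes of the neuropsychological assessment, followed by collaborative treatment goal setting". Allocation comes only after that session. Under Primary outcome measure, the goals are "evaluated by patients (of all study arms) in collaboration with the cognitive therapist at T1 and T2", by telephone.

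The section on the extensive programme says that the therapist assigns strategy modules according to the patient's cognitive profile and goals. The Discussion presents the basic version as a test of "if a low intensive, parsimonious approach that can be easily implemented and is inexpensive might be sufficient".

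**The concern.** The end of the Background foresees the programme becoming standard practice if it proves (cost-)effective, and the Discussion calls it a possible addition to standard care. The decision behind both statements is programme versus usual care. An ICUR labelled that way will be used for it.

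The trial holds assessment, feedback and goal setting constant across arms, so their cost and any benefit drop out of the increments. In the extensive arm the test profile and goals are also inputs to delivery. A service offering that programme as tested would have to provide them, yet the ICUR contains neither their cost nor their effect. For the basic arm, the result applies to an unguided programme whose users had all met a therapist and set goals first. A service offering the website alone would be offering something that the trial did not test.

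**Working it through.** The article states no ICUR, unit cost or QALY gain, so there is no figure to reproduce. The check is what each arm receives before the 26-week measurement (T2).

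| Step | Where stated | Basic | Extensive | Control |
|---|---|---|---|---|
| Online neuropsychological assessment, before allocation | Recruitment and randomization | yes | yes | yes |
| Therapist session: feedback and goal setting, before allocation | Recruitment and randomization | yes | yes | yes |
| Goal scoring with therapist at week 12 (T1) | Primary outcome measure | yes | yes | yes |
| Online programme before T2 | Intervention; Waiting list control group | yes | yes | no |

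The scoring call at T2 coincides with the last measurement and is left out.

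**What the ratio estimates.** Let dC and dQ be the incremental cost and QALYs of a programme arm against the trial's control. Let c and q be the cost and QALY effect of the shared pre-randomisation steps against usual care without them.

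- Trial ICUR = dC / dQ.
- Programme plus shared steps versus usual care = (dC + c) / (dQ + q).
- Net benefit not captured at ceiling L = L × q − c. It is zero when q = c / L.

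**Illustration.** All values of dC, dQ, c and q below are assumptions; only the ceiling is from the article. Take dC = EUR 300 and dQ = 0.01, so the trial ICUR is 300 / 0.01 = EUR 30,000. Let c run from EUR 0 to 400 and q from 0 to 0.01.

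- c = 0, q = 0.01: 300 / 0.02 = EUR 15,000.
- c = 250, q = 0.01: 550 / 0.02 = EUR 27,500.
- c = 250, q = 0: 550 / 0.01 = EUR 55,000.
- c = 400, q = 0: 700 / 0.01 = EUR 70,000.

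With dC = EUR 600 and dQ = 0.02 the trial ICUR is again EUR 30,000. The range becomes 600 / 0.03 = EUR 20,000 to 1,000 / 0.02 = EUR 50,000.

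At L = EUR 30,000 the break-even q is 100 / 30,000 = 0.0033 QALY for c = EUR 100, and 400 / 30,000 = 0.0133 QALY for c = EUR 400. A larger q would make the package look better than the trial ICUR suggests at that ceiling, and a smaller q would make it look worse. The article gives no basis for choosing between these cases.

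**The case against.** The strongest reply is that the parenthesis identifies the arm, and that the economic hypothesis in the Background is stated against the control group. Elements common to all arms should cancel from an incremental ratio. This stands: the randomised contrast is sound. A reader might infer that the ICUR is biased or invalid, but the documents do not support that. The fault lies in the name given to the comparator and the conclusion drawn from it.

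Further parts of the objection also stand:

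- **Not every shared contact is therapy.** The battery is self-administered online and serves as moderator and minimisation factor. The T1 call is described as scoring goal attainment. The feedback and goal-setting session carries most of the argument.
- **No one-directional figure is available.** A reader might infer that the plan understates cost per QALY by a known amount. That needs costs and utilities that the article lacks, and it ignores any benefit from goal setting.
- **The costs are not shown to be left out.** The cost list covers professional labour, staff training, administration and materials. It does not exclude the shared session, and such detail may sit in the full plan.
- **The basic arm is not misdescribed.** Having no guidance during the intervention is compatible with a session beforehand, and basic versus extensive is balanced on the shared steps.
- **Usual care might already contain these steps.** It is undefined, so this cannot be excluded. However, the Background calls evidence-based options limited, and nothing in the article suggests that usual care provides them.

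None of this makes the printed label right.

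**Conclusion.** The point holds as one about labelling and interpretation. The planned ICUR validly estimates each programme added to assessment, feedback and goal setting, compared with those steps followed by waiting. It is not an estimate against usual care, provided that usual care does not routinely include those steps. The size and direction of the gap cannot be determined from the document. The illustration shows only that the gap could fall on either side of the EUR 30k ceiling. The clinical hypotheses, the randomisation and the primary analysis are unaffected.

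**What to change.** 1. In the Cost-effectiveness section after Statistical analysis, replace the usual-care label for the control group with *waitlist control after neuropsychological assessment, therapist feedback and goal setting*.
2. Limit the cost-effectiveness conclusion to a programme preceded by those steps, and say so explicitly for the basic arm.
3. Record the cost per patient of the assessment and of the pre-randomisation therapist session. Add one ICUR scenario, with its acceptability curve, that charges this cost to the two programme arms: (dC + c) / dQ. Label it as cost-only. It pairs the package cost with an effect measured against controls who had the same steps, so it is conservative only if those steps bring no harm and cause no other net cost.
4. Do not extend the scenario to the ratio based on Goal Attainment Scaling (GAS), because patients without goal setting would have no GAS score. Do not charge the T1 scoring call as treatment.

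The cost is a wording change, slightly more costing work and one scenario ratio that will look less favourable than the main one. Recruitment, allocation and the main analyses stay as they are.
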